### Medical informatics and data management

The PopPK analysis will be performed with NONMEM [21-23]. The plasma concentration-time profiles for all constituents and derivatives of the Qishe pill will be described by a base structural model using the subroutine ADVAN5 [24]. The PK structural model will be parameterized in terms of apparent clearance and apparent distribution volume (CL/F and V/F), where F is the unknown oral bioavailability; the clearance and distribution volume are CL_M_ and V_M_, respectively. A Bayesian approach conditioned on the population characteristics will be used to estimate specific individual parameters. First-order conditional estimation methods (FOCE) and first-order conditional estimation methods with interaction (FOCE-I) will be tested during model development. The unexplained random variability in individual values of the structural model parameters will be described in the interindividual variability (IIV) model.

For the final model, a backward elimination process will be employed to identify significant covariates. The covariates in the full model will be excluded one by one. The objective function value (OFV) will be compared with that of the full model. A covariate will be retained in the model when its elimination results in an increase in the OFV of 7.88 (chi-square, *P* <0.005, *df* = 1). We will select the model according to the reduction in the OFV value, goodness-of-fit plots, reduction in the IIV of structure model parameters, residual error, robust model parameter estimation, and model stability. The architecture and basic elements of the PopPK research is illustrated in Figure 2.

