**Table 2 Tab2:** **Standard formula (capsule ingredients)***

**Chinese Name**	**Pharmaceutical Name**	**Powered Herb, %**
Huang Qi	*Radix Astragali*	28% (13g)
She Xiang	*Muscone*	0. (0.03g)
Chuan Xiong	*Szechuan Lovage Rhizome*	26% (12g)
Fang Ji	*Radix Stephaniae Tetrandrae*	19% (9g)
Qing Feng Teng	*Caulis Sinomenii*	26% (12g)
Niu Huang	*Calculus Bovis Artifactus*	0. (0.3g)

*Pharmaceutical terminology from Hsu [12].

With the high incidence of neck pain morbidity [13-16], and the wide variety of population properties (age, gender, weight, constitutional type, history of disease and life style, etc.) involved, providing an individual patient with optimal treatment at a given time is challenging. Therefore, personalized administration of the Qishe pill should be documented and practiced with multiple patients. Thus, a comprehensive research concerning the population pharmacokinetics (PopPK) of the Qishe pill in Chinese subjects should be conducted. In this study, we describe the population pharmacokinetic profile of the Qishe pill and compare its extent of metabolism in the three major constitution types (*Qi-*Deficiency, *Yin*-Deficiency and *Blood*-Stasis) to address major challenges of individualized and standardized Traditional Chinese Medicine into clinical practice, as a pilot trial.

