### Study population

#### Inclusion and exclusion criteria

We will recruit three main cohorts with confirmed *TCM* constitutional types: *Qi-*Deficiency (n = 36), *Yin*-Deficiency (n = 36) and *Blood-*Stasis (n = 36). All subjects will be 20 to 35 years old and with normal weight (18.5 kg/m^2^ ≤BMI <23.0 kg/m^2^). The detailed inclusion and exclusion criteria are presented in Table 3.

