### Highlights

Diagnosis and treatment based on an overall analysis of the illness and patient’s condition is the essence of the *TCM* theory. Rational medication is dependent upon a basic understanding of the way patients handle drugs (pharmacokinetics) and their response to specific drug effects (pharmacodynamics). Moreover, *TCM* constitutional types in traditional Chinese recipes could significantly influence the plasma concentration-time and their pharmacokinetic parameters after oral administration [38,39]. As data collection and OMICS analyses in PopPK of the Qishe pill will be processed simultaneously, research is focusing on the analyses of PK, OMICS and laboratory data to generate new hypotheses for translational research such as individualized dose, individualized scope of *TCM* and trial simulation.

The present study will establish three cohorts to detect potential differences in pharmacokinetic characteristics of the Qishe pill constituents in the three different *TCM* constitutional types, to assess whether the rate and extent of drug metabolism will be altered in *Qi-*deficiency or *Blood*-stasis constitutional types. If the differences in the Qishe Pill pharmacokinetics among the three major constitutional groups were known, personalized medication strategies for people with the three major constitutional types could be provided for the application of TCM.

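### The only stated covariate-retention rule does not exempt constitution type, the contrast the cohorts are recruited for; at a true P<0.005 an assumed 0.5-SD type effect would be dropped in about 64 to 83% of trials

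*Protocol article*

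**What the plan says.** **The rule.** In the protocol article, Medical informatics and data management, the final population model is reached by backward elimination from a full model: "The covariates in the full model will be excluded one by one". The criterion follows: "A covariate will be retained in the model when its elimination results in an increase in the OFV of 7.88", with the reference "chi-square, *P* <0.005, *df* = 1". The section lists no covariates and forces none into the model. It adds further grounds for choosing a model: "We will select the model according to the reduction in the OFV value, goodness-of-fit plots, reduction in the IIV of structure model parameters", followed by residual error, robust estimation and stability.

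**The purpose.** Under Inclusion and exclusion criteria: "We will recruit three main cohorts with confirmed" constitution types, 36 each. Under Highlights in the Discussion: "The present study will establish three cohorts to detect potential differences in pharmacokinetic characteristics of the Qishe pill constituents in the three different" constitution types, and the aim is "to assess whether the rate and extent of drug metabolism will be altered in" the Qi-deficiency or Blood-stasis type. The Background, after Table 2, names constitution type among the population properties that make individual treatment difficult: "age, gender, weight, constitutional type, history of disease and life style, etc". It also gives comparison of the three types as the aim, and calls the study a pilot trial.

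**The other route.** Pharmacokinetic parameters describes noncompartmental estimates (Cmax, AUC, half-life and others) but states no comparison between types.

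**The concern.** Deletion at P<0.005 is a reasonable way to thin out exploratory covariates. It is a poor way to handle the one factor on which subjects were recruited, because neither outcome gives a usable estimate of that factor.

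- **Type deleted.** The final model predicts the same typical CL/F and V/F in all three types. That is an implied ratio of 1 with no interval attached, even when the data are compatible with a sizeable difference.
- **Type retained.** The estimate appears only because it was large enough to pass a strict threshold, so on average it overstates the true difference.

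Highlights mentions individualized dose as a hypothesis to be generated, and personalised medication strategies as a possible later use. A result that is either set to zero or inflated is a weak basis for both.

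The degrees of freedom also matter. A three-level factor removed as a whole costs 2 df, whereas the stated 7.88 is a 1-df cut-off.

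**Working it through.** **1. The plan's own figure.** The upper 0.005 point of chi-square with 1 df is 7.879, and P(chi-square with 1 df > 7.88) = 0.0050. The stated 7.88 is correct for 1 df. With 2 df the 0.005 point is 10.60, and 7.88 corresponds to P = 0.019.

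**2. Inputs.** From the article: 36 per type, 108 in total, threshold 7.88. The article gives no effect size, SD or power; Study design bases the sample size on a guideline count of 8 to 12 subjects. Assumptions made here: a difference of 0.5 SD, where SD is the between-subject SD of the log parameter; each subject's parameter known without error; no other covariates.

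**3. Noncentrality** (differences in SD units).
- One type differs from the other two (means 0, 0, 0.5; overall mean 1/6): 36 × [2 × (1/6)² + (1/3)²] = 36 × 1/6 = 6.0. The matching 1-df contrast gives 0.25 × (36 × 72/108) = 6.0.
- Evenly spread types (means −0.25, 0, +0.25): 36 × 0.125 = 4.5. One pair of types, 36 against 36, on 1 df: 0.25 × 36/2 = 4.5.

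**4. Probability that the effect is dropped** = P(noncentral chi-square < cut-off).

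| Deletion | Cut-off | Actual level | Noncentrality 6.0 | Noncentrality 4.5 |
|---|---|---|---|---|
| 1 df | 7.88 | 0.005 | 64% (one type against two) | 75% (one pair) |
| 2 df, whole factor | 10.60 | 0.005 | 73% | 83% |
| 2 df, 7.88 taken literally | 7.88 | 0.019 | 56% | 68% |

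Hand check for one pair: SE = √(2/36) = 0.2357 SD; 0.5/0.2357 = 2.121; Φ(2.807 − 2.121) = Φ(0.686) = 0.754. The exact normal-model likelihood-ratio test gives 64.4% and 75.5% for the first row, 73.8% and 82.7% for the second, and 56.5% and 68.1% for the third.

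**5. Selection for size (one pair, 1 df).** To survive, the estimate must reach √7.88 × 0.2357 = 0.66 SD. Given survival, the mean estimate is 0.5 + 0.2357 × φ(0.686)/[1 − Φ(0.686)] = 0.5 + 0.2357 × 0.315/0.246 = 0.80 SD. Simulation gave 0.79 SD.

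**6. Sensitivity on the ratio scale.** With log-SD = √ln(1 + CV²), a true pairwise ratio of 1.25 is dropped at 1 df in 34% of trials at 30% CV, 79% at 50% CV and 90% at 70% CV. All three CVs are assumptions.

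**7. If type is kept regardless.** The 95% interval for a pairwise difference has half-width 1.96 × 0.2357 = 0.46 SD. At an assumed 50% CV (log-SD 0.472) this multiplies and divides the ratio by exp(0.46 × 0.472) = 1.24.

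**The case against.** The strongest reply is that the premise is inferred. The section names no covariate, the figure that shows the model's architecture is not available, and a condensed article may leave the covariate list and any forced terms to the full protocol or analysis plan. This stands as a limit on certainty. It does not remove the point, because the article does state a retention rule and applies it to the covariates of the full model without exception. With one pooled structural model, a type difference in CL/F or V/F has to enter as a covariate; separate models by type are not mentioned.

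Three stronger readings may tempt a reader, and the article does not support them.

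- **That type can be assessed only by passing 7.88.** Other model-selection criteria are listed, and the noncompartmental parameters could be compared by type. A full-model estimate with its uncertainty would also exist. None of these, however, is stated to secure an estimate of the type effect in the results.
- **That a dropped type will be reported as no difference.** No such reporting rule appears. Equal typical values are what the final model would imply, not what the authors say they will conclude.
- **That the miss rate at P<0.005 starts near 56%.** That figure belongs to 7.88 used on 2 df, where the level is 0.019.

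It can also be said that the study is called a pilot and that the 0.5 SD is not the sponsor's. Both are true. At 30% CV a ratio of 1.25 would be kept more often than dropped, so the size of the problem depends on variability that the article does not give.

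**Conclusion.** The point holds as a weakness in a stated analysis rule, conditional on constitution type being among the covariates tested, which is very likely but not written. Under the rule as it stands, the trial's main contrast is either removed from the final model or shown only when it is large.

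For a 0.5-SD difference with 36 per type, the effect is dropped in about 64 to 83% of trials at a true P<0.005. Within that range it is 75% for one pair at 1 df and 73 to 83% for the three-level factor at 10.60. Taking 7.88 literally on the 2-df factor gives 56 to 68%, but at P = 0.019. A surviving 1-df pairwise estimate averages about 0.8 SD when the truth is 0.5 SD.

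These figures rest on the assumed 0.5 SD and on error-free individual parameters; estimation error would raise the miss rates. This should be corrected before analysis, but it is not evidence that the authors plan to claim equality of the types.

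**What to change.** In Medical informatics and data management:

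1. State that constitution type is a prespecified three-level (2-df) effect on CL/F and V/F, and that it stays in the final model whatever its test result.
2. Report the between-type ratios with confidence intervals in every case.
3. State that failure to pass a retention threshold is not to be read as absence of a difference.
4. Confine the 7.88 rule to the other exploratory covariates that cost 1 df.

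An equivalence margin is optional and for the sponsor to choose. The article gives none, and a tight one would rarely be met. With 0.80 to 1.25 as an illustration, 50% CV and two truly identical types, a 95% interval would lie inside in about 4% of trials and a 90% interval in about 28%.

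The cost is wording and a few extra parameters (two coefficients each on CL/F and V/F); no new data are needed. The real downside is that the intervals will be wide, about ±0.46 SD for a pair at best, and many results will have to be called inconclusive.

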**Figure 2 Fig2:**
[figure not shown]
**Architecture and basic elements of the population pharmacokinetic (PopPK) research based on medical informatics and data management.**

## Discussion

Cervical radiculopathy is a significant public health problem worldwide, accounting for 60 to 70% of all cervical spondylopathy cases; it is generally believed that most symptoms can be cured or relieved by nonsurgical treatments [25].

Previous evidence-based trials have reported that analgesics and nerve-nutrition medicines have considerable effects on neck pain. Even though analgesics, such as aspirin, seem to be relatively safe, gastrointestinal reactions are often reported after their use [26]. Mecobalamin, a neuropathy drug, which relieves neck pain by stimulating the inhibition of nerve degeneration and improving the excitability of nerve fibers [27], seems to be ineffective when degeneration occurs.

The Qishe pill provides specific benefits for “Qi and Blood”, terms in *TCM*, meaning that it can profit and activate blood circulation. We have previously shown that the Qishe pill reversibly inhibits the NF-κB pathway, which might be an underlying mechanism behind its anti-inflammatory potential in disc degeneration *in vivo* [28]. Extensive investigations have confirmed that the Qishe pill has several therapeutic features, inhibiting platelet surface activity and platelet aggregation [29], reducing the synthesis and release of local PGE [30], decreasing malondialdehyde content in inflammatory exudates [31], and inhibiting the IL-1beta-induced phosphorylation of extracellular signal-regulated kinases 1/2 and c-Jun N-terminal kinase [32]_._ These effects include predictable pharmacokinetics (PK) and pharmacodynamics (PD) behaviors; in addition, the Qishe pill suppresses acute inflammatory reactions and pain events with fewer gastrointestinal discomfort and rash. A simple and sensitive method using ultra-high-performance liquid chromatography–tandem mass spectrometry (UHPLC–MS/MS) on a reverse-phase C18 column was developed for the simultaneous determination of the 19 major components of the Qishe pill [20]. This method was successfully validated for the quantification of the 19 components in the Qishe pill products, and constitutes a new standard in quality assessment of TCM prescriptions containing multiple bioactive components (see Additional file 1). Over the last few years, several interactions between the Qishe pill ingredients and the pharmacokinetics of flavonoids (calycosin and calycosin-7-o--d-glycoside), alkaloids (tetrandrine, fangchinoline, magnoflorine and berberine hydrochloride), ferulic acid and glycosides (astragaloside IV, astragalussaponin I and III) have been reported [20,33-37]. Furthermore, HPLC-TQ/MS was employed to detect the component contents in the Qishe pill, whose partial pharmacokinetic parameters are shown in Table 5.

**Table 5 Tab5:** **Pharmacokinetic parameter after oral administration of Qishe pill at a dose of 6.33 g•kg-1 to SD rats (mean ± SD, n = 6)**

**Parameters**	***SEA***	***SEI***	***FOR***	***ONO***	***5-O-M***	***AST-IV***
***t*** _1/2_ **(h)**	22.72 ± 11.49	12.35 ± 10.3	51.24 ± 44.19	7.04 ± 3.7	42.79 ± 16.29	11.41 ± 12.51
***C*** _max_ **(ng/ml)**	53.71 ± 16.14	136.51 ± 45.24	9.39 ± 4.32	2.45 ± 1.51	0.14 ± 0.07	13.3 ± 5.42
***T*** _max_ **(h)**	0.22 ± 0.07	0.31 ± 0.16	0.22 ± 0.07	0.25 ± 0.00	0.25 ± 0.00	2.00 ± 2.25
***AUC*** _last_(h*ng/ml)	606.87 ± 161.89	851.3 ± 251.31	38.1 ± 8.04	4.17 ± 1.53	1.13 ± 0.10	107.74 ± 65.65
***AUC*** _tot_(h*ng/ml)	826.3 ± 229.51	900.76 ± 236.67	71.57 ± 26.49	4.89 ± 1.65	2.31 ± 0.41	129.75 ± 61.01
***MRT*** **(h)**	36.54 ± 15.27	16.58 ± 6.89	70.4 ± 60.63	9.55 ± 4.04	65.96 ± 20.60	17.9 ± 17.38
***CL*** **(L/h/kg)**	0.05 ± 0.01	0.02 ± 0.01	0.02 ± 0.00	0.12 ± 0.05	0.16 ± 0.03	0.06 ± 0.07
***V*** **z (L/kg)**	1.41 ± 0.67	0.41 ± 0.33	0.98 ± 0.43	1.12 ± 0.83	9.38 ± 2.09	0.83 ± 0.94

In the pre-trial of limited size (n = 6), accordingly, a UPLC-TQ/MS method for simultaneous determination of plasma concentrations of 15 bio-active Qishe pill constituents was developed and validated. The results showed that the method was selective, sensitive, precise, accurate, and reliable for comparative quantification of ferulic acid, calycosin, calycosin glycosides,calycosin-7-O-β-glucoside, ononin, formononetin, astragaloside, tetrandrine, fangchinoline base, berberine, tetrahydroberberine, tetrahydropalmatine, sinomenine and magnolia base, in human plasma samples. The mean plasma concentration–time profiles of the major bio-active components determined after oral administration of Qishe pills are illustrated in Figure 3.

**Figure 3 Fig3:**
[figure not shown]
**Mean plasma concentration-time curves of seven components after oral administration of the Qishe pill at medium and high dosages (n = 4).**

According to the results of the pilot trial, further research should be conducted with modified protocol in dosage setting, requirements of sample collection (diet specifications, blood-collection time window) and sample processing.

### Highlights

Diagnosis and treatment based on an overall analysis of the illness and patient’s condition is the essence of the *TCM* theory. Rational medication is dependent upon a basic understanding of the way patients handle drugs (pharmacokinetics) and their response to specific drug effects (pharmacodynamics). Moreover, *TCM* constitutional types in traditional Chinese recipes could significantly influence the plasma concentration-time and their pharmacokinetic parameters after oral administration [38,39]. As data collection and OMICS analyses in PopPK of the Qishe pill will be processed simultaneously, research is focusing on the analyses of PK, OMICS and laboratory data to generate new hypotheses for translational research such as individualized dose, individualized scope of *TCM* and trial simulation.

The present study will establish three cohorts to detect potential differences in pharmacokinetic characteristics of the Qishe pill constituents in the three different *TCM* constitutional types, to assess whether the rate and extent of drug metabolism will be altered in *Qi-*deficiency or *Blood*-stasis constitutional types. If the differences in the Qishe Pill pharmacokinetics among the three major constitutional groups were known, personalized medication strategies for people with the three major constitutional types could be provided for the application of TCM.

## Trial status

Participant recruitment and prescreening began in December 2014. Blank control serum samples have been collected for standardization of the general methodology and normal conditions.

## Abbreviations

AST-III: Astragaloside III
AST-IV: Astragaloside IV
*AUC*: area under the plasma concentration–time curve
BER: Berberine
CA: Cholic acid
CCS: Calycosin
CCSG: Calycosin-7-O-β-D- glucoside
CE: Collision energy
*C*_max_: Maximum plasma concentration
DF: Distribution volume
CL/F: Apparent clearance
CL_M_: Clearance
DAI: Daidzein
FAN: Fangchinoline
FOCE: First-order conditional estimation methods
FOCE-I: First-order conditional estimation methods with interaction
FOR: Formononetin
GA: Gallic acid
*k*_e_: Elimination rate constant
MS: Mass spectrometry
MRM: Multiple reaction monitoring
NMR: Nuclear magnetic resonance
OFV: Objective function value
ONO: Ononin
PAL: Palmatine
PD: Pharmacodynamics
PK: Pharmacokinetics
PopPK: Population pharmacokinetic
SEA: Senkyunolide A
SEI: Senkyunolide I
SIN: Sinomenine
TCM: Traditional Chinese Medicine
*T*_max_: Time to maximum concentration
UHPLC–MS/MS: Ultra-high-performance liquid chromatography–tandem mass spectrometry
V/F: Apparent distribution volume
V_M_: Distribution volume
5-O-M: 5-O-methylvisammioside
